### Participants

#### Inclusion and exclusion criteria

Our participants are enrolled as outpatients in the orthopedic clinic of the Heidelberg University Hospital and participate in a four-week outpatient multidisciplinary pain treatment including physiotherapy, ergotherapy, music and dance therapy, individual and group psychotherapy. As such, theyhave experienced chronic pain for at least six monthsare between 18 and 80 years of agehave previously received standard treatment consisting of at least one rehabilitation program or two inpatient treatments, which did not yield lasting effects.

Exclusion criteria includehigh C-reactive protein (CRP) levels as an indicator of rheumatoid arthritisacute inflammations of the spinea tumora diagnosed psychosisa diagnosis of a bipolar or neurological disorderan insufficient ability to communicate in German

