### Sample size calculation

We calculated the necessary sample size for each of our two subsamples (intervention and control) with the G*Power Analysis software program for two-sample t-tests [17], and by reference to our primary outcome measure (pain intensity). Based on the results of our pretests, we expected a small to medium effect of 0.4 for the comparison of the two groups (with an alpha level = 0.05, two tailed, β = 0.2). Results indicate that at least 93 participants are required for each group, for a total of 186.

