### Statistical analysis

Descriptive statistics will be used to describe the characteristics of the study sample. Analysis of variance will be used for the evaluation of the changes of the continuous outcomes pain intensity and physical functioning (T1-T2, T1- T3). Research condition (attachment style and study group), will be used as independent variable. Demographic variables such as sex, age, education and clinical variables such as opioid intake and comorbidity will be entered as covariates. Partial regression coefficients will be used to determine if the “working alliance” mediates the effect of attachment on the continuous outcomes (pain and physical functioning).

Missing data on the questionnaires will be handled according to the questionnaire protocol.

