### Potential limitations

We do not believe that two training sessions for the therapeutic team will suffice to yield large effects on therapeutic outcome. However, we expect that the constant exchange within the team during weekly team meetings and monthly supervision sessions will facilitate the development of a clear understanding of attachment styles as well as a repertoire of methods to deal with incidents, which are critical for the working alliance. Therefore, therapists are likely to become more seasoned in recognizing and dealing with the attachment behavior of their patients in the course of the study. As a result, effects might only become apparent in an advanced phase of data collection for the intervention group.

Patients with a preoccupied attachment style and, even more pronounced, the ones with a fearful attachment style, gain the least from the state-of-the art multidisciplinary pain treatment. These patients are known to have difficulty with the regulation of distance and proximity to other people. Our program in the outpatient clinic offers many opportunities to express distancing or proximity-seeking behavior in dealing with doctors, physiotherapists, psychologists and the group of other patients and therefore provides many chances for difficulty. Even if the therapeutic team is trained in attachment concepts, the time frame might not be enough to use this new knowledge to their advantage. It is very likely that in such a setting, patients with insecure attachment patterns will at some point elicit (negative) reactions either from staff or from other patients similar to the ones they continuously experience in their every-day lives. This would confirm their general expectations of themselves and others in relationships, hereby reinforcing these expectations.

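### The sample size and the ANOVA treat patients as independent although part of the programme is delivered in groups nested within study block; if outcomes within a group are correlated, the type I error exceeds 5%

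*Protocol article*

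**What the plan says.** All references are to the protocol article.

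- **Inclusion and exclusion criteria:** patients "participate in a four-week outpatient multidisciplinary pain treatment including physiotherapy, ergotherapy, music and dance therapy, individual and group psychotherapy". Individual and group elements are mixed. Group size, fixed or changing membership, and common or rolling start dates are not described.
- **Potential limitations:** the programme involves "dealing with doctors, physiotherapists, psychologists and the group of other patients". The authors think it very likely that insecurely attached patients will provoke negative reactions from staff or other patients, which would reinforce these patients' expectations of relationships.
- **Design and Trial status:** the two blocks run one after the other. Control recruitment began in March 2012, with pre- and post-treatment assessments complete by October 2013 (184 patients received T1). The intervention block ran from March 2014 to December 2015 (194 received T1).
- **Sample size calculation:** done with the "G*Power Analysis software program for two-sample t-tests", "with an alpha level = 0.05, two tailed, β = 0.2". The authors write that "we expected a small to medium effect of 0.4 for the comparison of the two groups" and conclude that "at least 93 participants are required for each group, for a total of 186". No design effect is mentioned.
- **Statistical analysis:** "Analysis of variance will be used" for the changes in pain intensity and physical functioning. The factors are attachment style and study group, and the covariates are patient-level. No therapy-group or cohort term is named.

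**The concern.** A two-sample t-test and an ordinary ANOVA both assume that each patient's outcome is independent of every other's, given the model terms. Patients who share group psychotherapy over the same weeks share a group climate, and the article itself treats contact with fellow patients as relevant to how treatment goes.

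The sequential design makes this matter for the main comparison. No therapy group contains both control and intervention patients, so variation between groups does not cancel out of the intervention contrast. With a positive ICC, the true variance of that contrast is larger than the one the ANOVA estimates. Confidence intervals are then too narrow, and a difference between blocks is declared significant too often. Recruiting more therapy groups of the same size makes the estimate more precise but leaves the unadjusted test just as anti-conservative.

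**Working it through.** **Step 1: the plan's own figure.** Inputs from the sample size section: d = 0.4, two-sided alpha 0.05, power 0.80, equal groups.

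- Normal approximation: n = 2 × ((1.960 + 0.842)/0.4)² = 98.1, so 99 per group.
- Exact noncentral t: 100 per group.
- Power at the stated 93 per group: 77.9% (normal) or 77.4% (t).

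The stated 93 is not reproduced. It would need d of about 0.413. This shortfall exists with an ICC of zero and is separate from clustering.

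**Step 2: a plausible cluster size.** The article gives none, so I derive a rough one from the trial status section. Counting both end months, the blocks span about 20 and 22 months, which is 21.7 and 23.9 four-week slots.

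- 184/21.7 = 8.5 and 194/23.9 = 8.1, so about 8.3 per slot.
- At the planned 93 per group over the same slots: 93/21.7 = 4.3 and 93/23.9 = 3.9, so about 4.1.

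These are averages per calendar slot, not documented therapy groups. I therefore use a range of m = 4 to 12. The ICC range of 0.01 to 0.10 is also an assumption.

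**Step 3: type I error of the unadjusted test.** The design effect is DE = 1 + (m − 1) × ICC. The true two-sided error is 2 × (1 − Φ(1.96/√DE)).

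| m | ICC 0.01 | ICC 0.05 | ICC 0.10 |
|---|---|---|---|
| 4 | DE 1.03, 5.3% | DE 1.15, 6.8% | DE 1.30, 8.6% |
| 8.3 | DE 1.07, 5.8% | DE 1.37, 9.3% | DE 1.73, 13.6% |
| 12 | DE 1.11, 6.3% | DE 1.55, 11.5% | DE 2.10, 17.6% |

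Worked case, m = 8.3 and ICC 0.05: DE = 1 + 7.3 × 0.05 = 1.365, √DE = 1.168, 1.96/1.168 = 1.678, error 9.3%. A correct interval would be about 17% wider than the unadjusted one.

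**Step 4: power of a cluster-adjusted test at d = 0.4** (normal approximation, cluster size matched to sample size, ICC 0.01/0.05/0.10).

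- 93 per group, m = 4.1: 77/72/66%, against 78% with no clustering.
- 184 and 194, m = 8.3: 96/91/84%, against 97% with no clustering.
- 184 and 194, most extreme case (m = 12, ICC 0.10): 76.5%, the only combination in the range that falls below 80%.

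Dropout would lower the last two lines. Its numbers are in a figure that is not shown.

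**The case against.** The strongest case against has four parts.

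**Closed cohorts are not documented.** A reader might infer that patients pass through the four weeks together as fixed groups. The article does not say so. It describes a mixed individual and group programme, and with rolling entry a patient has no single treatment group. This stands. It is why the cluster size is a range and why calendar month is only a proxy.

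**The correlation is not shown.** A reader might infer that standard errors are too small and that the 5% level fails as a matter of fact. Both require a positive ICC, and none is given. The passage on reactions from fellow patients is about individual attachment behaviour as much as about shared outcomes. At an ICC of 0.01 the excess is small. This also stands, so the conclusion must be conditional. The passage still gives a reason not to assume that the ICC is zero.

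**Power is not the issue it may seem.** A reader might blame clustering for the failure to reach 80%. But 93 per group gives only about 77% with no clustering, and about twice the planned number received T1. At those numbers power stays above 80% for nearly all assumed values, before dropout. The power claim therefore does not carry the point.

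**Staff effects and scope.** The personnel of one clinic treat both blocks, so staff effects are largely crossed with arm and need not shrink the standard error. The point rests on patient groups and cohorts only. It can also be said that random-effect structures belong in an analysis plan. But the article does not leave the model open. It names an ANOVA and a t-test calculation, and both make an independence assumption that sits badly with its own description of the programme.

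**Conclusion.** The point holds in conditional form. Neither the sample size nor the named analysis allows for correlation between patients treated together, and the sequential blocks put all of any such correlation into the intervention contrast. If the ICC is positive, the unadjusted intervals are too narrow and the type I error is above 5%: about 5.3% to 17.6% over assumed clusters of 4 to 12 and ICCs of 0.01 to 0.10, and about 9% at roughly 8 per slot with an ICC of 0.05. If the ICC is zero, nothing is lost.

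The documents do not establish closed cohorts, a group size or an ICC, and they do not support attributing the shortfall from 80% power to clustering alone. What remains is a concern about type I error and interval width that a larger sample does not repair. The change should be made, but the point does not show that the trial is underpowered or that its results would be wrong.

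**What to change.** **Statistical analysis section:** for the study-group comparison, replace the plain ANOVA with a linear mixed model that keeps the stated factors and covariates and adds a random intercept for therapy group. If entry is rolling, use the start-month cohort instead. Use Satterthwaite or Kenward-Roger degrees of freedom and report the estimated ICC. State how patients enter the programme and how large the therapy groups are. About 45 four-week slots (21.7 + 23.9) should be enough to estimate the extra variance component.

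**Sample size section:** state that the calculation assumes independent patients. Keep the discrepancy between 93 and the 99 to 100 that the inputs require as a separate correction, and do not explain it by clustering.

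**Cost:** one model term and one data field. It needs each patient's therapy group or start date, which the article does not mention but which a clinic would normally hold. Confidence intervals become somewhat wider (about 17% at a design effect of 1.37). With rolling entry, calendar month is only a proxy for who was treated with whom and may capture only part of the correlation.

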### Ethics statement

The study procedures were approved by the Institutional Review Board of the Medical Faculty, University of Heidelberg (S-305/2013). As such, they comply with the ethical standards established in the Declaration of Helsinki and with the guidelines of ICH-GCP. Upon arrival at the department, the principal investigator verbally states the study purpose and procedures to eligible patients and informs them about their right of withdrawal at all times. Additionally, all participants obtain an information sheet on the study objectives and modalities, data preparation and pseudonymized data storage. All participating patients provide written informed consent.

### Sample size calculation

We calculated the necessary sample size for each of our two subsamples (intervention and control) with the G*Power Analysis software program for two-sample t-tests [17], and by reference to our primary outcome measure (pain intensity). Based on the results of our pretests, we expected a small to medium effect of 0.4 for the comparison of the two groups (with an alpha level = 0.05, two tailed, β = 0.2). Results indicate that at least 93 participants are required for each group, for a total of 186.

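### The sample size of 93 per group does not follow from its printed inputs, which need 100 per group; at 93 the power is about 77%, not 80% (minor)

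*Protocol article*

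**What the plan says.** The section "Sample size calculation" of the protocol article gives every input that the calculation needs.

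- Test and software: the number was obtained "with the G*Power Analysis software program for two-sample t-tests".
- Effect: "we expected a small to medium effect of 0.4 for the comparison of the two groups", which the section attributes to pretests.
- Error rates: "with an alpha level = 0.05, two tailed, β = 0.2".
- Result: "Results indicate that at least 93 participants are required for each group, for a total of 186".

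The outcome used for sizing is pain intensity. The section states no dropout allowance, no covariate adjustment and no other design factor, and it presents 93 as the direct output of the calculation.

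The "Trial status" section adds that 184 control patients and 194 intervention patients received the T1 questionnaire.

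**The concern.** With the test, effect, alpha, sidedness and power all printed, any reader with the same software can repeat the calculation, and the answer is not 93. The printed effect needs more patients than the section asks for, so 93 per group carries less power than the stated beta implies. This is the only sample size justification in the document. The section calls 93 a minimum, and at the printed effect that minimum misses the stated power.

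**Working it through.** **Inputs** (all from "Sample size calculation"): two-sample t-test; effect 0.4; alpha 0.05, two-tailed; beta 0.2, so power 0.80; equal groups. One reading is needed: 0.4 is taken as the standardised mean difference d. That is the effect size G*Power takes for this test, and it fits the section's description of the effect as small to medium.

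**Step 1: attempt to reproduce 93.**

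Normal approximation: n per group = 2(z₀.₉₇₅ + z₀.₈₀)² / d² = 2 × (1.960 + 0.842)² / 0.4² = 2 × 7.849 / 0.16 = 98.1, so 99.

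Exact t-test: find n such that a noncentral t variable with 2n − 2 degrees of freedom and noncentrality d√(n/2) exceeds the two-sided critical value with probability 0.80. The solution is n = 99.08, so **100 per group, 200 in total**. Neither method gives 93.

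**Step 2: power at the stated size and near the required one (exact t, d = 0.4).**

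| n per group | Noncentrality 0.4√(n/2) | Degrees of freedom | Power |
|---|---|---|---|
| 93 | 2.728 | 184 | 77.4% |
| 99 | 2.814 | 196 | 79.97% |
| 100 | 2.828 | 198 | 80.4% |

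The normal approximation gives 77.9% at 93. The gap is 100 − 93 = 7 per group (14 in total) and 80 − 77.4 = 2.6 percentage points of power.

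**Step 3: look for a variant that gives 93.**

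| Variant | n per group | Agrees with the text? |
|---|---|---|
| One-sided 0.05, 80% power | 78 | No: text says two-tailed |
| One-sided, 15% dropout, 78/0.85 | 92 | No: two-tailed, and no dropout rate stated |
| One-sided, 20% dropout, 78/0.80 | 98 | No: same reasons |
| One-sided, 85% power | 91 | No: contradicts two-tailed and beta 0.2 |
| Mann-Whitney under normality, 99.08/0.955 | 104 | No: text names the t-test |
| Paired t-test | 52 pairs | No: text says two-sample |

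None gives 93, and those that come near it contradict the text. A dropout allowance on the two-sided result would only raise the number above 100.

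**Step 4: solve for the effect.** With 93 per group, two-sided 0.05 and 80% power, the exact detectable effect is d = 0.4130. With 92 per group it is 0.4153. So a calculation that rounds n up returns 93 for d between about 0.413 and 0.415.

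**Step 5: practical size.** With 184 and 194 patients all analysed and d = 0.4, exact power is about 97%. To fall below 100 analysed, the loss would have to exceed 1 − 100/184 = 46% of controls or 1 − 100/194 = 48% of the intervention group.

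**The case against.** The strongest defence is rounding. The effect is printed to one decimal and is said to come from pretests, so the underlying estimate need not be exactly 0.400. Values that print as 0.4, from 0.35 up to 0.45, give between about 130 and 79 per group, and 93 lies inside that range. This stands as a possible explanation. The document does not state it, so the section as printed still does not reproduce, and if rounding is the cause the remedy is to print the value used.

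The second defence is that the gap hardly matters here, because about twice either figure received T1. This also stands. The T1 counts are not the analysed counts: the planned analysis of variance uses T1-T2 and T1-T3 changes, and the dropout figure is not shown. But nothing visible suggests that the analysed numbers fall between 93 and 99, the only range in which the two thresholds would disagree.

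A reader might go further and infer that T2 and T3 completeness will be judged against a threshold set too low, or that the trial is underpowered. The document supports neither. No section uses 93 as a completeness criterion, a stopping rule or a condition for analysing follow-up data, and enrolment did not stop there. The calculation is also a planning approximation based on an unadjusted t-test, whereas the planned analysis includes covariates, so a hard cut-off at 100 would claim more precision than it has.

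**Conclusion.** The concern holds as a reporting inconsistency of minor severity. With 0.4 read as a standardised difference and taken at face value, the printed inputs require 100 per group (200 in total) rather than 93 (186), and 93 per group gives 77.4% power. The result does not depend on the method, since the normal approximation also exceeds 93, at 99.

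The check cannot say which figure is at fault. The effect may be a rounded 0.413 to 0.415, or the sample size may be wrong. It would therefore be too strong to say that both the power and the minimum number are in error. No effect on enrolment, analysis or interpretation is shown. The figure of about 97% power assumes that all T1 patients are analysed, and the analysed numbers are not visible.

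**What to change.** Change one sentence in "Sample size calculation", in whichever of these ways matches what was done:

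- if the effect was exactly 0.4, state the requirement as 100 per group, 200 in total; or
- keep 93 per group and state the power as about 77% at an effect of 0.4; or
- if the pretest effect was rounded, print the unrounded value that yields 93 (about 0.413 to 0.415).

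The cost is the edit itself and, under the first two options, a slightly less favourable figure. No additional enrolment, no change to the analysis and no new completeness rule for T2 or T3 is called for.

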### Statistical analysis

Descriptive statistics will be used to describe the characteristics of the study sample. Analysis of variance will be used for the evaluation of the changes of the continuous outcomes pain intensity and physical functioning (T1-T2, T1- T3). Research condition (attachment style and study group), will be used as independent variable. Demographic variables such as sex, age, education and clinical variables such as opioid intake and comorbidity will be entered as covariates. Partial regression coefficients will be used to determine if the “working alliance” mediates the effect of attachment on the continuous outcomes (pain and physical functioning).

Missing data on the questionnaires will be handled according to the questionnaire protocol.

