Attachment-based Working Alliance Model

Patients in the intervention group, who receive an attachment-based multidisciplinary treatment, will report a larger mean reduction of the pain intensity between pre-treatment and post-treatment assessments than patients in the control group, who receive the state-of-the-art multidisciplinary treatment. It is expected that this larger reduction of the pain intensity in the intervention group compared to controls can be specifically attributed to better outcomes for the intervention group patients than control group patients who have been assessed with insecure attachment styles. Moreover, patients with an insecure attachment style and patients with more attachment anxiety are expected to report higher levels of pain intensity as well as physical functioning.The intervention is specifically designed to improve the therapeutic relationship and to hereby improve treatment outcomes. Therefore, we expect to find improved ratings of the relationship (working alliance) between patients and therapists in the intervention group which will mediate the treatment outcomes pain intensity and physical functioning.There will be a greater decline in help-seeking behavior and use of medication in the intervention group compared to the control group from pre-treatment to after the 6-month follow-up. This will be especially hypothesized for insecurely attached patients in the intervention group.Subjective self-awareness of the patients particularly with regard to self-esteem will be expected to change to a greater extent in the intervention group compared to the control group.

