## Methods

### Design

The study is conducted in a block design with two patient groups as blocks (baseline, attachment intervention) and 3 assessments T1, T2, and T3 (before treatment, post-treatment, and at a 6 month follow-up). We decided against a randomized controlled trial because (a) we had ethical concerns with a design that would put patients on a waiting list for several months, and (b) a block design ensures that the intervention’s effects only influence the outcomes of the treatment group: After collection of data for the control group, the health care personnel of the outpatient pain clinic receives training sessions on attachment theory and its use in the therapeutic context. These training sessions will not be carried out until data collection for the control group will be complete. More attachment-related training sessions alternating with supervision meetings will be held on a monthly basis to assist the therapeutic team in the practical application during data collection for the second sample, the treatment group. During our weekly team meetings, the case reviews will be complemented with a discussion on the individual attachment style of each patient. Also these meetings will be used to collect situations, which are perceived to be critical for the forming of a working alliance by the therapeutic team (for example, situations in which the patient misses entire therapeutic sessions or appears too late to them on a regular basis). These critical situations will be subsequently used to structure the discussions of individual cases in the bi-monthly training sessions.

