## Conclusions

### Trial status

Recruitment of patients for the control group started in March 2012. Pre- and post-treatment assessments were complete by Oct. 2013 with a total of 184 patients who received a questionnaire at T1 (for an overview of the recruitment process including dropout numbers, see Fig. 3). The 6-month follow-up questionnaires of the control group were completely sent out by May 2014. Each team member received monthly intervention training sessions between Nov. 2013 and May 2015. For an overview of the received attachment training, see Table 2. Recruitment of patients for the intervention group started in March 2014. Pre- and post-tretments were complte by Dec. 2015 with a total of 194 patients who received T1. The 6-months follow-up questionnaires of the interventions group will be completely sent out by June 2016.

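### The change-score analysis does not name the T1 value of the outcome as a covariate, which costs precision and, under a common slope, lets an observed T1 gap between the blocks shift the contrast

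*Protocol article*

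**What the plan says.** The Statistical analysis section of the protocol article fixes three parts of the model.

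- **Dependent variable:** "Analysis of variance will be used for the evaluation of the changes of the continuous outcomes pain intensity and physical functioning", for T1-T2 and for T1-T3.
- **Factors:** "Research condition (attachment style and study group), will be used as independent variable".
- **Covariates:** "Demographic variables such as sex, age, education and clinical variables such as opioid intake and comorbidity will be entered as covariates".

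No other section adds the T1 value of the outcome to the covariates. Table 1 marks pain and physical functioning at T1, T2 and T3, so the value is available.

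The main hypothesis, at the end of the Background, is itself about change: intervention patients "will report a larger mean reduction of the pain intensity between pre-treatment and post-treatment assessments than patients in the control group".

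On allocation, the Design section says: "We decided against a randomized controlled trial". The Trial status section dates the start of recruitment to March 2012 for controls and March 2014 for the intervention block.

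**The concern.** A raw change score gives the T1 value a fixed coefficient of 1. An analysis with T1 as a covariate estimates that coefficient from the data. If the T1-T2 correlation is below 1 and the variances are similar, the fixed coefficient is too large and the error variance is larger than it need be.

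The second issue is specific to this design. Patients enter a block by date of admission, and nothing in the design balances T1 pain between the blocks. If a block happens to start with worse pain and part of that is transient, its patients will on average fall back further, and a raw change score counts this as improvement. At stake are power for the primary comparison and, under the conditions set out in the working, a shift that is not small beside the planned effect of 0.4.

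**Working it through.** **Inputs from the protocol article.** Standardised effect 0.4, two-sided alpha 0.05, beta 0.2 and 93 per group (Sample size calculation). The text does not say whether 0.4 is in SDs of the score or of the change.

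**Assumptions, not in the document.** T1-T2 correlation rho of 0.3 to 0.7; T1 gap D between blocks of 0.1 to 0.3 SD; score SD of 1 at both times.

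**The plan's own figure.** A two-sample t-test with these inputs needs 99.08, so 100 per group, not 93. At 93 per group its power is 0.774. That discrepancy is a separate matter; 0.774 is used below only as the starting point.

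**Precision.**
- Variance of the change: 2(1-rho).
- Residual variance after adjusting for T1: 1-rho².
- Ratio: (1-rho²) / [2(1-rho)] = (1+rho)/2.

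If 0.4 is in SDs of change, the effective standardised effect after adjustment is 0.4 / √ratio. The third column uses the t-test. The last uses the normal approximation and takes 0.4 in SDs of the raw score.

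| rho | Variance ratio | Power at 93, SDs of change | Power at 93, SDs of score |
|---|---|---|---|
| 0.3 | 0.65 | 0.774 → 0.920 | 0.635 → 0.816 |
| 0.5 | 0.75 | 0.774 → 0.880 | 0.779 → 0.883 |
| 0.7 | 0.85 | 0.774 → 0.837 | 0.941 → 0.969 |

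These figures compare models without other covariates. If opioid intake and comorbidity already explain part of T1 pain, the added gain is smaller. Correlation between T1 and block costs a variance factor of 1 + D²/4, which is 1 + 0.04/4 = 1.01 at D = 0.2.

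**Shift from an observed T1 gap.** Suppose both blocks come from one population with a common slope rho and the intervention has no effect. A block whose T1 mean is D higher then has a T2 mean that is rho × D higher. Its mean reduction is larger by D - rho × D = (1-rho) × D.

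The last column is the probability that the nominal 5% change-score test rejects in either direction at 93 per group, given that gap. The test uses SE √[2(1-rho) × 2/93], while the contrast varies around (1-rho)D with SD √[(1-rho²) × 2/93].

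| D (SD) | rho | Shift (SD) | Rejection rate given D |
|---|---|---|---|
| 0.1 | 0.3 / 0.5 / 0.7 | 0.07 / 0.05 / 0.03 | 0.028 / 0.035 / 0.041 |
| 0.2 | 0.3 / 0.5 / 0.7 | 0.14 / 0.10 / 0.06 | 0.077 / 0.071 / 0.064 |
| 0.3 | 0.3 / 0.5 / 0.7 | 0.21 / 0.15 / 0.09 | 0.176 / 0.140 / 0.104 |

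At D = 0.2 the shift is 35%, 25% or 15% of an effect of 0.4 score SDs. For scale, the standard error of a chance T1 difference at 93 per group is √(2/93) = 0.147 SD.

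**The case against.** **The list is open.** The covariates are given as examples, so T1 pain or T1 ODI could be meant. This stands: the text supports only that T1 is not named. A reader might infer that it is excluded; the document does not say so. The point is still more than missing detail, because the article states the dependent variable and the model, and the most useful covariate for that model is left to choice.

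**Bias.** A reader might infer that any T1 imbalance biases the raw change. The document does not support that. If the blocks are one population, imbalance is chance and the change-score test keeps its nominal error rate on average; the shift exists only given an observed gap. If the blocks are stably different populations, (1-rho)D no longer applies. Change scores are then right under parallel trends, and adjustment for an error-prone T1 rating can itself be biased. This is Lord's paradox. One clinic and one set of eligibility criteria make the first case plausible but do not establish it.

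**The hypothesis concerns reduction.** True, but with T1 in the model the study-group coefficient is the same whether the dependent variable is the change or the later value. The objection does stand for attachment style: the Background expects higher pain in insecurely attached patients, so adjusting for T1 changes what that contrast estimates.

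**Opioid intake.** A reader might infer that a post-treatment value would be used, since medication is recorded at T1 and T3. The article does not say which is meant, so this is unstated detail and not an error.

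**Conclusion.** The point holds as a recommended improvement to the stated model. It does not show that the planned analysis is invalid.

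The precision gain is the firmer part. With equal variances it exists for every rho below 1: 15% to 35% less variance over the assumed range, less whatever the other covariates already explain. The power rise to 0.84-0.92 further requires that 0.4 is in SDs of change.

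The shift is conditional on one source population, a common slope and an observed gap. The article reports no T1 difference between the blocks, so its size here is unknown. A gap of 0.1 SD would do little harm to the error rate; 0.3 SD would raise it to 0.10-0.18.

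It would be wrong to conclude that adjusting for T1 repairs the lack of randomisation. The blocks began recruiting two years apart, and confounding by period remains under either analysis.

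**What to change.** In the Statistical analysis section, name the T1 value of the analysed outcome (T1 VAS for pain, T1 ODI for physical functioning) as a covariate in the study-group comparison at T2 and at T3. Report the unadjusted change score as a sensitivity analysis. State that any disagreement between the two will be interpreted with caution, because they then answer different questions. For the attachment-style contrast, note that adjusting for T1 changes the estimand, and say which version answers the hypothesis.

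The cost is one degree of freedom per model and reliance on a common slope; no new data are needed. Trial status reports pre- and post-treatment assessments as complete in both blocks, so this would be a late change to the stated model. It should be dated and its timing relative to any group comparison recorded. Reporting both analyses keeps the stated one visible.
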